### 2.3. Study procedures and visit schedule

Participants will be recruited consecutively according to eligibility criteria. Patients will be invited by physicians from the research team during routine clinical practice. Healthy controls will be invited by members of the research team and, if they agree to participate, will be referred to a physician from the research team for baseline assessment. As this is an observational study, no randomization or blinding procedures will be applied.

At the baseline visit (V0), all participants will receive verbal and written information about the study objectives, methodology, non-invasive nature of the procedures, confidentiality safeguards, and exclusive research use of the collected data. Written informed consent will be obtained before any study-related procedure. A clinical interview will then be conducted to collect baseline sociodemographic and clinical information, followed by psychometric assessment using the clinical instruments specified in the protocol. During the same session, voice recordings will be obtained under standardized conditions.

Only patients with depressive disorder will undergo longitudinal follow-up. Patients will attend four additional visits coinciding, whenever possible, with routine psychiatric follow-up visits: V1 at 30 days, V2 at 60 days, V3 at 90 days and V4 at 120 days, each with an allowed window of ±7 days. At each follow-up visit, the same recording and clinical assessment procedures applied at baseline will be repeated. Clinician-rated and self-reported measures of depressive severity will be updated, and relevant clinical changes, including treatment adjustments or adverse events, will be documented. Healthy controls will complete only the baseline visit under the same recording conditions.

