In all participants, data collection will be integrated into the clinical interview. Only the part of the medical interview corresponding to the MADRS assessment will be audio recorded. In order to combine open ended questions by clinicians that allow patients to describe their experiences in their own words, allowing spontaneous and elaborated responses, while adopting a reliable method of exploration, the instructions of Montgomery and Asberg for the MADRS will be adopted, moving from broadly phrased questions about each symptom to more detailed ones which allow a precise rating of severity [27]. The recorded material will comprise the complete MADRS-related clinical interaction, including an initial free-speech segment immediately followed by the semi-structured questions used to complete the scale. The free-speech segment will be an introductory part of the recorded MADRS assessment (namely, patients will be asked to describe, in their own words, how they have been feeling in the past week). This recorded segment is expected to last approximately 10–30 minutes including the initial free-speech segment, allowing voice and speech to be collected within a clinically meaningful interaction while maintaining a standardized procedure.

Voice recordings will be assigned a pseudonymized audio identifier linked to participant type, participant code and visit number. Any relevant recording incident, including interruption due to patient need, clinical need or technical problems, will be documented in the case report form and considered in data quality assessment.

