### 2.5. Voice recording protocol

Voice recordings will be obtained using a Jabra Speak 510 USB omnidirectional microphone, positioned frontally at a distance of no more than 20 cm from the participant’s mouth. Recordings will be conducted in a quiet hospital room, with minimized background noise, closed doors and windows whenever feasible, silenced electronic devices, and no overlapping speech or external interruptions whenever possible.

The Jabra Speak 510 microphone was selected for pragmatic and translational reasons: it is affordable, widely available, easy to deploy and compatible with routine hospital use. This choice prioritizes ecological validity over laboratory-grade audio fidelity, which may reduce the precision of signal-sensitive measures such as jitter, shimmer, HNR, and intensity. This potential variability will be reduced by maintaining the same microphone, configuration, placement, and recording conditions throughout the study. This approach is consistent with previous studies that have used non-specialized recording devices, including tablet microphones, smartphone microphones and mobile phones, to extract clinically relevant speech and voice features [19,24,25,30].

Repeated assessments will be scheduled within a similar time-of-day window for each participant whenever feasible. Because recordings are integrated into routine clinical visits, exact consistency cannot be guaranteed; recording time will therefore be documented and considered in sensitivity analyses. Audio recordings will be stored in uncompressed WAV format to preserve signal integrity during feature extraction. All files will be labeled using pseudonymized alphanumeric identifiers. Speaker diarization will identify participant and interviewer segments, followed by manual review. Overlapping or uncertain segments will be excluded, and the original recording will be preserved unchanged. For acoustic and paralinguistic analyses, only participant speech will be retained. The complete interaction will be automatically transcribed and manually reviewed to correct transcription and speaker-attribution errors. Linguistic variables and contextual text embeddings will be extracted from the reviewed participant transcripts, while interviewer turns will be retained as conversational context.

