### 2.6. Variables

All study variables will be recorded in a pseudonymized case report form developed specifically for the VOICE-DEP study. Variables will be classified into: (i) baseline variables collected only at V0, and (ii) longitudinal visit variables collected at V0, V1, V2, V3 and V4 in patients with depressive disorder.

Exposure variable: The main exposure variable is the medical diagnosis of moderate or severe unipolar depressive disorder, with or without psychotic symptoms, according to the predefined ICD-10 categories included in the protocol.

Primary outcome variables: The primary outcome variables are the standardized voice recording and the multimodal speech- and speech-derived variables extracted from the recorded clinical interview. These variables will be grouped into acoustic, paralinguistic and linguistic domains.

Clinician-rated and self-reported symptom variables: At each study visit, depressive symptom severity and global clinical status will be assessed concurrently with the voice recording using the MADRS, the Clinical Global Impression scale (CGI), and the Patient Health Questionnaire-9 (PHQ-9). These variables will provide the clinical reference outcomes for cross-sectional and longitudinal analyses. Psychotic depression, operationally defined by an ICD-10 diagnosis of F32.3 or F33.3, will be recorded as a binary clinical variable. The same clinician-rated and self-reported assessments will also be conducted in healthy controls at baseline (V0) to identify possible subthreshold symptoms.

Baseline and longitudinal variables: Baseline variables collected at V0 will include demographic, anthropometric, clinical and contextual information, including psychiatric and medical history, substance use, stressful life events, and previous depressive episodes. Longitudinal variables collected across visits will include recording traceability variables, symptom scales, pharmacological treatment variables, psychotherapy variables and neurostimulation-related variables.

Metadata related to the recording process, including pseudonymized audio identifiers and recording incidents, will also be documented for traceability and quality control purposes.

The complete list of study variables operationalized in the VOICE-DEP case report form is summarized in Table 2. The list of multimodal voice- and speech-derived variables is summarized in Table 3.

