Neurostimulation variables	Receipt of electroconvulsive therapy in the current episode, type of electroconvulsive therapy, and other neurostimulation treatments	V0–V4 in patients

**Table 3 pone.0353827.t003:** Multimodal voice- and speech-derived variables predefined in the VOICE-DEP protocol.

Domain	Variable/ group of variables	Operationalization/ measurement
Acoustic	Pitch	F0 mean, standard deviation and range (Hz).
	Energy/ intensity	Mean and standard deviation (dB).
	MFCCs	Coefficients 1–13 summarized by mean and standard deviation.
	Harmonic-to-noise ratio	dB.
	Jitter	Percentage (%).
	Shimmer	Percentage (%).
	Spectral descriptors	Spectral centroid, roll-off and slope (Hz or normalized units).
	Formants	F1–F3 mean frequency and bandwidth (Hz).
	Spectral/ prosodic entropy	Dimensionless entropy index.
	Embedding-based acoustic features	High-dimensional vector representations derived from pretrained models (e.g., Wav2Vec2, HuBERT).
Paralinguistic	Speech rate/ articulation rate/ pause duration	Words per second and pause duration in seconds.
	Prosodic range	F0 and intensity variability (Hz, dB, or coefficient of variation).
	Pause ratio	Silence-to-speech proportion (0–1 or %).
Linguistic	Sentiment polarity	Continuous score from −1 to +1.
	Negative emotional word ratio	Percentage (%) of negatively valenced words.
	First-person singular pronouns	Percentage (%) or frequency per 100 words.
	Lexical diversity	MTLD, Honor´e and type-token ratio.
	Word count/ mean sentence length	Number of words and words per sentence.
	Lexical sentiment variance	Standard deviation of sentiment scores.
	Lexical coherence/ cohesion	Cosine similarity based on semantic embeddings.
	Contextual text embeddings	High-dimensional representations extracted from a pretrained open-weight language model.

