The study is conducted in a single clinical center and focuses on Spanish-speaking participants, which may induce selection bias and restrict external validity across healthcare systems, dialects, or linguistic contexts. Dialectal variation across Spanish-speaking regions may influence acoustic, prosodic, and linguistic characteristics. Therefore, the findings will be interpreted within the linguistic and geographical context of the study population and will require future external validation in samples from other Spanish-speaking regions and sociolinguistic settings. However, this focus also addresses a relevant gap in the literature, which has been predominantly centered on English-language datasets.

Because of the observational design and treatment heterogeneity, changes in speech cannot be fully disentangled from the effects of specific treatments. Treatment-related analyses will therefore remain exploratory and will not support causal inference.

Residual variability related to the recording time of the day will be acknowledged as a study limitation.

Finally, clinician-administered scales are used as the primary reference standards, but they are themselves subject to measurement variability and do not constitute an objective ground truth. In addition, symptom-focused MADRS questions may influence some linguistic variables, particularly sentiment-related measures, which will therefore be interpreted cautiously. The present protocol does not aim to replace clinical judgment but rather to complement it by identifying speech-derived markers that correlate with established measures of depressive severity.

In summary, the formal clinical diagnosis will define the study groups, whereas the MADRS, CGI, and PHQ-9 will be used to quantify symptom severity and longitudinal change. Speech-derived measures will therefore be interpreted as complementary correlates of clinical assessment rather than as independent objective standards, under the premise of supporting, but not replacing, the clinical judgment.

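### Linguistic features come from the whole MADRS interview, so interview length and topic cannot be separated from depressed speech, and no stated analysis controls for length

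*Protocol article*

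**What the plan says.** Section 2.3 limits the audio recording to the MADRS part of the interview, in patients and controls alike: "The recorded material will comprise the complete MADRS-related clinical interaction, including an initial free-speech segment immediately followed by the semi-structured questions". Questioning proceeds by "moving from broadly phrased questions about each symptom to more detailed ones which allow a precise rating of severity". Length is not fixed: "This recorded segment is expected to last approximately 10–30 minutes including the initial free-speech segment". The interviewer knows the participant's group, since "no randomization or blinding procedures will be applied".

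Section 2.5 gives the source of the text features: "Linguistic variables and contextual text embeddings will be extracted from the reviewed participant transcripts". It states no restriction to the opening segment. Its only length rule is a minimum of two minutes of valid participant speech. It also has total duration, valid participant-speech duration and number of transcribed words documented for each recording.

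Table 3 (section 2.6) predefines sentiment polarity, negative-word ratio, MTLD, Honoré's statistic, type-token ratio, coherence, and length itself ("Number of words and words per sentence"). Section 2.7 makes AUC the principal metric for patients versus controls, compares audio, text and combined models, and relates the features to MADRS, CGI and PHQ-9.

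Section 3.1 accepts that the interview may make content, duration and topic coverage vary. It adds that "symptom-focused MADRS questions may influence some linguistic variables, particularly sentiment-related measures, which will therefore be interpreted cautiously".

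**The concern.** The conversation that yields the predictors also yields the MADRS score, and its subject is the symptoms that distinguish the groups. A participant who reports little may be asked little more; one who reports a symptom will usually be asked to describe it. If so, length and topic of the transcript follow symptom state through the interview procedure, apart from any change in how a depressed person speaks.

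Three results are exposed:

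- **Patient-control differences and AUC** on length- or topic-dependent features.
- **Secondary objective iii**, the added value of combining modalities, because the text models carry the content of the answers to the severity questions.
- **Associations with MADRS**, at one visit or over time within a patient, because the same answers set the score.

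Section 2.4 says the pilot evaluates standardization and analytical validity. Whether a feature measures speech or the interview is a question of exactly that kind, so the exploratory label does not settle it.

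**Working it through.** **1. The plan's own figure.** Section 2.4 gives d = 0.70 for 25 versus 50, two-sided alpha 0.05, 80% power. Normal approximation: d = (1.960 + 0.842) × √(1/25 + 1/50) = 2.802 × 0.245 = 0.686. The noncentral t gives 0.695. The stated figure is correct and serves as the yardstick below.

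**2. Length alone, for word count.** The protocol gives no lengths by group, so this step rests on assumptions: participant words are proportional to recording length, length is log-normal with the same spread in both groups, and 10–30 minutes is read in three ways. Then SD(log length) = ln 3 / k, length ratio for a given d = exp(d × SD), and AUC = Φ(d/√2).

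| 10–30 min read as | k | SD (log) | Ratio giving d = 0.70 | d at ratio 1.10 | d at 1.25 | d at 1.50 |
|---|---|---|---|---|---|---|
| ±2 SD | 4 | 0.275 | 1.21 | 0.35 | 0.81 | 1.48 |
| 5th–95th percentile | 3.29 | 0.334 | 1.26 | 0.29 | 0.67 | 1.21 |
| ±1 SD | 2 | 0.549 | 1.47 | 0.17 | 0.41 | 0.74 |

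A difference of 21% to 47% in length gives d = 0.70, with AUC = Φ(0.70/1.414) = 0.69. The calculation is symmetric. If patients say less, the matching shortfalls are 1 − 1/1.212 = 0.17 to 1 − 1/1.469 = 0.32. A 10% difference matters much less.

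**3. Length alone, for type-token ratio.** With vocabulary growing as a power β of text length, the ratio scales as r^(β−1) when length changes by a factor r. For r = 1.25 and assumed β of 0.5 to 0.7, that is 0.894 to 0.935, a fall of about 6% to 11%. A simulation with one Zipf-type vocabulary shared by every speaker gave mean values of 0.58 at 500 words, 0.50 at 1,000, 0.41 at 2,000 and 0.37 at 3,000.

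Next, 25 patients were compared with 50 controls (300 repetitions, controls centred on 1,000 words, SD of log length 0.275):

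| Length ratio | Rejected at 0.05 | d | AUC |
|---|---|---|---|
| 1.00 | 4% | −0.01 | 0.50 |
| 1.25 | 85% | 0.77 | 0.71 |
| 1.50 | 100% | 1.33 | 0.83 |

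Every simulated speaker has the same vocabulary, so these d and AUC values leave out real differences between people. Those would widen the spread and reduce both figures. The table shows that length alone can separate the groups, not how far it will.

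**4. What the plan does about length.** The two-minute minimum excludes very short recordings but sets no cap, fixed window or adjustment. Section 2.5 records durations and word counts, but section 2.7 names no model that uses them to control for length. Among the lexical-diversity measures, MTLD is less length-dependent, but it stands beside the other two without priority.

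**The case against.** The strongest reply has five parts.

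- **Symptom-dependent probing is not written down.** Section 2.3 describes detailed questions about each symptom, with no rule that stops early when a symptom is absent. This stands: deeper questioning of patients is an inference, though a plausible one.
- **The direction is unknown.** The 10–30 minutes include interviewer turns and pauses, and depressed patients may speak less. This stands too. A reader might infer that the AUC is inflated and the comparison tilted towards text; the documents do not support a fixed direction. Nor may the two ends of the single range be treated as patient and control means, since nothing suggests a threefold group difference.
- **The groups are defined by ICD-10 diagnosis, not by MADRS.** So circularity in the strict sense applies to the MADRS associations. For the AUC the problem is confounding with the interview.
- **The plan already responds.** Section 3.1 names content, duration and topic as sources of variability, and its caution covers linguistic variables beyond sentiment. Lengths are recorded, audio and text are modelled separately, Shapley-based attribution is planned, and classifier results are called exploratory. These steps would help reveal reliance on length. But section 3.1 treats it as variability rather than a possible difference between groups, and neither caution nor attribution separates the two sources in a fitted model.
- **Such detail may sit in an analysis plan not shown.** Fair for details of windowing. But the article itself fixes the speech task, the text source and the length-dependent features, and it is that combination which causes the difficulty.

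**Conclusion.** The concern holds in a limited form. As the plan is written, results on raw word count, whole-text type-token ratio and Honoré's statistic mix interview length with depressed speech, and results on sentiment and negative-word ratio mix in topic. The text-versus-audio comparison and the MADRS associations inherit this. If group lengths differ by 21–47%, depending on the assumed spread, length alone yields d = 0.70 for word count; if they differ by about 10% or less, the effect is modest. Actual lengths by group are not in the protocol, and the sign of the bias is open.

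A reader might go further and conclude that these features detect the questionnaire and not depression. The documents do not support that: the features carry both, MTLD is less affected, and acoustic, rate and pause measures are not counts of length. The d = 0.70 sensitivity statement is unaffected.

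**What to change.** 1. Compute type-token ratio, Honoré's statistic and coherence on a fixed number of participant words, and name MTLD as the main lexical-diversity measure.
2. Mark the end of the free-speech segment during the manual review already planned. Pre-specify, as a sensitivity analysis, the same unimodal and multimodal models on that segment, with its own minimum length. Report whether the added value of text persists there.
3. Report models with and without raw word count, plus a benchmark classifier that uses only the speech duration and word count already recorded under section 2.5. Keeping both versions preserves any real signal from reduced speech output.

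The cost is one time mark per recording and a second run of the pipeline. Original recordings are kept unchanged, so sessions already collected can be marked too, but only until the recordings are destroyed, no later than 1 January 2030. The shorter segment will give noisier features, and some segments will not be evaluable. The opening prompt also asks about feelings, so it equalizes the prompt without fully removing the effect of topic on sentiment; the caution in section 3.1 should stay.

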### 2.4. Sample size and sampling strategy

The planned study sample comprises 75 participants: 25 patients with a clinical diagnosis of moderate or severe unipolar depression and 50 healthy controls. Patients will be assessed at five time points: baseline (V0) and four monthly follow-up visits at 30, 60, 90 and 120 days, each with an allowed window of ±7 days. Assuming complete follow-up, this will generate 125 longitudinal voice recordings in the clinical group. Healthy controls will undergo a single baseline assessment, generating 50 voice recordings. The planned dataset therefore comprises 175 voice recordings.

The sample size was defined pragmatically as a feasible recruitment target for a hospital-based feasibility and methodological pilot study conducted in a real-world clinical setting. The study is not intended as a definitive diagnostic accuracy trial powered to estimate the performance of a final clinical classifier. Rather, it is designed to evaluate the feasibility, standardization, reproducibility and analytical validity of a multimodal voice- and speech-based methodology for depression assessment and longitudinal monitoring.

As a quantitative sensitivity analysis, a baseline comparison of 25 patients and 50 healthy controls, with a two-sided significance level of 0.05 and 80% power, would detect a standardized mean difference of approximately Cohen’s d = 0.70. The study is therefore primarily sensitive to moderate-to-large effects. This is presented as a sensitivity analysis because reliable prospective effect-size estimates are not available for the multiple exploratory speech-derived variables included.

The sampling strategy will be consecutive and non-probabilistic. Eligible patients will be recruited during routine clinical care in the Department of Psychiatry, including both outpatient consultations and inpatient care. Healthy controls will be invited by members of the research team and assessed after confirmation of eligibility.

Although a balanced baseline comparison between patients and healthy controls would be methodologically desirable, the final allocation was defined according to feasibility considerations. Healthy controls will be individually matched to patients by age and sex whenever feasible. If individual matching cannot be achieved, control recruitment will be guided by the age and sex distribution of the patient group to obtain group-level frequency matching as closely as possible. Recruitment of clinically characterized patients with moderate or severe depressive disorder is expected to be more demanding because it requires repeated clinical assessments and longitudinal follow-up. In contrast, healthy controls require only a single baseline visit, allowing the inclusion of a larger control group without substantially increasing study burden. Therefore, the study will include 25 patients and 50 healthy controls. This design is expected to strengthen the baseline characterization of non-depressed speech patterns while preserving the longitudinal focus of the clinical cohort.

At participant level, baseline analyses will compare patients and healthy controls, whereas longitudinal analyses will focus on within-patient changes across repeated assessments. For predictive modeling, the imbalance between groups will be explicitly considered through appropriate analytical strategies, such as participant-level data splitting, balanced resampling, class weighting or sensitivity analyses when applicable.

Given the pilot nature of the study and the moderate sample size, classifier performance estimates will be interpreted as exploratory and hypothesis-generating. The study will prioritize transparent feature extraction, reproducible preprocessing, clinically interpretable modeling and longitudinal within-subject analysis over the development of a definitive deployable diagnostic model. Model complexity will be limited in relation to the available sample size, and classifier performance estimates will be accompanied by confidence intervals whenever feasible.

